## Abstract

**Background:**

Although various placebo acupuncture devices have been developed and used in acupuncture research, there is controversy concerning whether these devices really serve as appropriate placebos for control groups.

**Methods/Design:**

The proposed study is a single-center prospective random sequence participant- and assessor-blinded trial with two parallel arms. A total of 76 participants will be randomly assigned to Group 1 or Group 2 in a 1:1 ratio. Group 1 will consist of Sham Streitberger’s needle, Real Streitberger’s needle, and Phantom acupuncture session. Group 2 will consist of Park Sham device with real needle, Park Sham device with sham needle, and no treatment session. Participants will have a total of three acupuncture sessions in a day. The primary endpoint is blinding test questionnaire 1. Secondary endpoints are the Bang’s blinding index, the Massachusetts General Hospital Acupuncture Sensation Scale index, and physiological data including heart rate, heart rate variability, and skin conductance response.

**Discussion:**

This trial will evaluate the relevance of using placebo acupuncture devices as controls using a validation test procedure.

**Trial registration:**

Clinical Research Information Service: KCT0001347.

## Background

Acupuncture is a treatment modality that has been used in Eastern Asia for more than 2000 years. An increased interest in the clinical effects of acupuncture has also been expressed in the West in recent years. In a 1997 report on the effects of acupuncture, the National Institutes of Health (NIH) stressed the need for evidence of efficacy [1]. Subsequently, the number of randomized controlled clinical trials (RCTs) using acupuncture to treat various conditions has rapidly increased; however, many acupuncture clinical trials have methodological limitations. Establishing appropriate placebo control groups is one of several issues. Ideally, placebo acupuncture should satisfy two conditions: (1) it should be indistinguishable from real acupuncture to blinded participants, and (2) it should be physiologically inert. Various placebo acupuncture devices that satisfy these conditions have been developed and used in acupuncture clinical trials.

Currently, there are two types of acupuncture controls: (1) sham acupuncture, in which real acupuncture needles are inserted into the skin either fully at non-acupuncture points or superficially at acupuncture points, non-acupuncture points, or non-relevant acupuncture points with certain conditions, and (2) placebo acupuncture, which uses non-penetrating acupuncture devices (i.e., blunt tip needles or non-needle devices) [2].

Various non-penetrating placebo acupuncture devices such as Streitberger’s needle, the Park sham device (PSD), and the Takakura needle have been developed. The first device, Streitberger’s needle, was developed in 1998 and used a plastic ring covered with a plastic sheet to place the needle [3]. When the practitioner taps the needle, it moves inside the handle and appears as if the acupuncture needle punctures the skin. However, it does not puncture the skin, but only a pricking sensation is felt by the patient because the tip is blunt.

In 1999, Park et al. developed the PSD which was similar to Streitberger’s needle [4]. The PSD included a flange with adhesive tape and a guide tube to place the placebo needle on the acupuncture point, while Streitberger’s needle used a plastic ring and sheet. Although these two placebo acupuncture devices were successfully applied to blinded participants and their use validated, there still remains the limitation that they induce physiological activity by touching the skin.

In 2014, Lee et al. developed a novel form of placebo acupuncture, phantom acupuncture, which induces participant expectation without any tactile stimulation such as palpation, needle insertion, or manipulation and which was also validated using blinded participants [5]. However, complex equipment is needed to perform phantom acupuncture. Therefore, it may be difficult to apply phantom acupuncture in clinical acupuncture trials.

Although various placebo acupuncture devices have been developed and used in acupuncture research, there is controversy concerning whether these devices are really appropriate for placebo control groups.

This trial will evaluate various placebo acupuncture devices that have been used in acupuncture clinical trials using a validation test to determine if they are suitable to be used in control groups.

## Methods/Design

### Objectives

The objectives of this trial are to evaluate the validity of different types of placebo acupuncture devices and determine their suitability for use as placebos in clinical trials.

### Trial design and study setting

This study will be a single center, prospective, randomized, random sequence, participant and assessor blinded trial with two parallel arms.

We will conduct the study in the Kyung Hee University Medical Center.

There are arm1 (Group1) and arm2 (Group2) in our trial that is separated. Each group has three different intervention sessions in random sequence. The order of intervention will be randomized.

### Inclusion and exclusion criteria

Participants who meet the following criteria will be included irrespective of previous acupuncture experience: (1) healthy participants 20–50 years old, and (2) participants who can communicate and complete the questionnaire.

Participants will be excluded if they meet any of the following criteria: (1) individuals who have taken medications during the prior month that could influence trial results (e.g. medications for epilepsy, depression, panic disorders, schizophrenia, etc.), (2) pregnant or breast-feeding women, (3) Korean Medicine Doctors (KMD) or Korean Medicine University students (because we think that they can distinguish between placebo and real acupuncture better than the general population), (4) individuals who drank alcohol or coffee, or overworked the day before or the day of the experiment, and (5) individuals who are determined to be unsuitable for following the study protocol by the researcher.

### Recruitment

We will upload an advertisement to the hospital and university homepages, and place a poster advertisement on the bulletin boards of the hospital and university. Potential participants will call the clinical research coordinator (CRC) and will be pre-screened for eligibility. Eligible participants will make an appointment. When potential participants visit the hospital, the investigator will provide information about volunteering and explain the risks and benefits of the research. When the individuals agree to enroll in the research, they will sign an informed consent form.

### Randomization and allocation concealment

After signing the informed consent form, the participants will be randomized to Group 1 or Group 2. Group 1 will receive the Real Streitberger’s needle (Real ST), Sham Streitberger’s needle (Sham ST), and Phantom acupuncture (PHNT); Group 2 will receive the PSD with a real needle (Real Park), the PSD with a sham needle (Sham Park), and no treatment (No treat). The treatment orders in both groups will be randomized. A computerized balanced block randomization will be performed by an independent clinical research coordinator (CRC) using R version 3.1.2 with ‘block random’ function. The CRC will send an e-mail regarding the name, random number, and treatment order of enrolled participants to the practitioners and operators. This e-mail will be documented in the trial master file (TMF).

### Blinding

Participants will be blinded in this trial. However, it is almost impossible to blind practitioners and operators because they need to know which acupuncture devices to use. They will not be allowed to communicate with the participants concerning the type of acupuncture devices and the purpose of the study. Outcome assessors and statisticians will also be blinded to treatment allocation.

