### Intervention

#### Study flow

The study flow will be as follows. Group 1 will consist of Sham ST, Real ST, and PHNT. Group 2 will consist of Real Park, Sham Park, and No treatment. Groups 1 and 2 are separate groups; participants allocated to Group 1 will not receive Real Park, Sham Park, and No treatment and vice versa. Participants will have a total of three sessions (acupuncture or no treatment) in a day (Fig. 1). Before acupuncture treatment, the investigator will explain to participants that they will receive three different types of acupuncture except for the no treatment session. Participants will not know that placebo acupuncture occurred until all sessions are completed. To avoid order effect, the order of the three treatment sessions in each group will be randomly assigned by the CRC. Before the first session, the CRC will collect demographic information (e.g., age, sex) and baseline data (e.g., vital signs, acupuncture expectation questionnaire (AEQ) [6], and bodily sensation questionnaire (BSQ)). After each treatment session, participants will complete the blinding test questionnaire 1 (BTQ 1) and acupuncture sensation questionnaire (ASQ) and will be asked about adverse events (AEs). After completion of the third BTQ 1 and ASQ, an independent assessor will inform the participants of the use of placebo acupuncture and instruct them to complete the blinding test questionnaire 2 (BTQ 2).

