#### Phantom acupuncture and no treatment session

In PHNT, practitioners will not provide any tactile stimulation and will only approach their hand to the left ST 36 acupuncture point without touching. A recorded video clip of the participant’s Real ST session will be played during the PHNT session. If the PHNT session is scheduled as the first session, we will play a video from another participant with similar skin color and leg hair.

In the No treatment session, practitioners will inform participants that they will not receive any treatment. A blinding questionnaire will not be completed; recorded physiological data will be used as a baseline. In order to ensure comparability, participants will undergo the same procedure except they will be shown a 3 min video clip that is not related to acupuncture but has a similar background color and shows some type of artificial movement that would occur with same stimulation time point during an acupuncture session.

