### Outcome measurement

#### Primary endpoint

BTQ 1 : After each acupuncture session, participants will complete the BTQ 1. BTQ1 consists of five questions. If a participant completes all five questions without any doubt or asking, we will conclude blinding is succeeded. If participants mention strange aspect of the questionnaire or reply they did not receive acupuncture treatment, conclude that blinding is failed. Otherwise, we will conclude that blinding is succeeded.

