### Statistical analysis

As our design has two independent groups that acquire comparability by randomization, we can compare variables not only within each group, but also between groups.

The primary outcome of our research will be to compare the blinding rates of the placebo acupuncture devices studied within and between groups. We will also conduct several exploratory secondary outcome analyses. Expectation for acupuncture (measured by AEQ) [6], previous acupuncture experiences, and age will be considered as covariates. We will analyze physiological data in three tonic responses (before, during, and after acupuncture) and during phasic responses. We will not statistically compare the Bang’s BI [9]. Instead, we will calculate the point estimate and 95 % confidence interval of Bang’s BI.

For dichotomous variables (i.e., blinding rate), within group comparison will be performed using Cochran’s Q test for Group 1 (Sham ST, Real ST, and PHNT) and McNemar’s test for Group 2 (Sham, Real Park). We will not check the blinding of the No treatment session. Comparisons of blinding rates between group devices (Sham ST vs Sham Park or PHNT vs Sham Park) will be performed using the chi-square test, and comparisons within group devices (PHNT vs Sham ST) will be performed using McNemar’s test. For continuous variables (i.e., the MASS index, De-qi sensation, physiological data such as HR, HRV, and SCR), within group comparisons will be performed using repeated measured ANOVA for Group 1 and paired *t*-test for Group 2. We will use the independent *t* test for comparisons between group.

When we analyze physiological data, we will use the both change ratio contrast to baseline and absolute value. Change ratio and absolute value of HR and SCR will be compared for three separate windows during the tonic responses (before vs during vs after acupuncture session). As absolute change value is very dependent on baseline value, it will be used as covariates.

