### Safety and adverse event outcomes

When each session is completed, the assessor will ask if any AE occurred and it will be documented in the CRF. If any AEs occur, the type of AE, start/end date, severity, manner of report, course, outcome, causality with acupuncture treatment, and actions taken will be documented and appropriate treatment will be provided to the participants.

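### The article claims blinding of assessors and statisticians to allocation, but the design does not keep the group masked; this exposes only the between-group comparisons of blinding rates

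*Protocol article*

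**What the plan says.** All places are in the protocol article.

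- **Blinding:** "Outcome assessors and statisticians will also be blinded to treatment allocation". No level (group, order or device) is named as an exception.
- **Randomization and allocation concealment:** "After signing the informed consent form, the participants will be randomized to Group 1 or Group 2". The order of the three sessions is also randomized. Only Group 2 has a No treatment session.
- **Primary endpoint:** "After each acupuncture session, participants will complete the BTQ 1". The scoring rule includes: "If participants mention strange aspect of the questionnaire or reply they did not receive acupuncture treatment, conclude that blinding is failed".
- **Phantom acupuncture and no treatment session:** for No treatment, "A blinding questionnaire will not be completed; recorded physiological data will be used as a baseline". Participants are told in that session that they will not be treated.
- **Statistical analysis:** "We will not check the blinding of the No treatment session". Blinding rates are tested by Cochran's Q across three conditions in Group 1, by McNemar's test across two in Group 2, and by chi-square between devices of different groups.
- **Safety and adverse event outcomes:** contact with participants is described in these words: "When each session is completed, the assessor will ask if any AE occurred and it will be documented in the CRF".
- **Study flow:** "After completion of the third BTQ 1 and ASQ, an independent assessor will inform the participants of the use of placebo acupuncture". No exception is made here for Group 2.

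**The concern.** The Blinding section claims a safeguard that other sections of the article undo at the level of group. The missing form after No treatment marks a participant as Group 2, and a third form marks a participant as Group 1. An assessor who questions participants after every session will also speak to people who have just been told they received no treatment. The statistician sees three blinding columns in one group and two in the other.

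This matters because BTQ 1 is the primary endpoint and is not wholly mechanical. Someone must decide whether a remark, doubt or query counts as failed blinding. If that person knows the group, the comparison of blinding rates across groups could reflect how remarks were counted as well as how the devices performed.

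**Working it through.** **The plan's own figure.** The Sample size calculation takes 30 per session and about 20% drop-out: 30 / (1 − 0.20) = 37.5, rounded up to 38 per group, and 2 × 38 = 76 participants. This reproduces, and nothing below changes it.

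**Forms by design, with complete data.**
- Group 1: three acupuncture sessions, so 38 × 3 = 114 forms.
- Group 2: two acupuncture sessions, so 38 × 2 = 76 forms.
- Total: 114 + 76 = 190 forms.

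**What the form count reveals depends on how forms are scored.** The article does not state this, so three cases are set out.

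1. *A participant's forms are scored together.* Three forms mean Group 1 and two mean Group 2. The group is identified for every complete record.

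2. *Each form is handled when completed, by someone following the participant.* Assume 1:1 allocation and No treatment equally likely to be first, second or third. The probability that a Group 2 participant has had no omitted form is 2/3 after session 1, 1/3 after session 2 and 0 after session 3. By Bayes' rule, the probability of Group 1 given a form after every session so far is:
   - after one form: 0.5 / (0.5 + 0.5 × 2/3) = 0.60
   - after two forms: 0.5 / (0.5 + 0.5 × 1/3) = 0.75
   - after three forms: 0.5 / (0.5 + 0) = 1.00

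   Forms for which the group is certain when they are handled:
   - Group 1: the third form only, 1 of 3 per participant, so 38 × 1 = 38 forms.
   - Group 2: forms that follow No treatment. These number 2, 1 or 0 when No treatment is first, second or third, a mean of (2 + 1 + 0) / 3 = 1 of 2, so 38 × 1 = 38 forms.
   - Together: (38 + 38) / 190 = 76 / 190 = 40%. (This 76 counts forms; that it equals the number of participants is coincidence.)

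3. *Forms are separated and scored singly without identifiers.* The count reveals nothing.

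**What the count does not reveal.** In none of the three cases does it show which Group 1 form belongs to Real ST, Sham ST or PHNT, or which Group 2 form belongs to Real Park or Sham Park.

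**Which planned comparisons are exposed.**

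| Comparison (Statistical analysis) | Within or between groups | Exposed by this route? |
|---|---|---|
| Cochran's Q, Group 1 | within | no |
| McNemar, Real Park vs Sham Park | within | no |
| McNemar, PHNT vs Sham ST | within | no |
| Chi-square, Sham ST vs Sham Park | between | yes |
| Chi-square, PHNT vs Sham Park | between | yes |

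**A textual conflict alongside.** Study flow places disclosure after a third BTQ 1 for all participants. The No treatment and Statistical analysis sections leave Group 2 with only two.

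**The case against.** The strongest reply is that the article never says who scores BTQ 1, when, or whether forms stay linked. The assessor named for adverse events need not be the scorer, and Study flow names an independent assessor only for the final disclosure and BTQ 2. Scoring details may lie in the full protocol or the operating procedure. This stands. A reader might infer that blinding of the primary endpoint is impossible, or that the group is always known before forms are scored. The document does not support either reading, because scoring single de-linked forms would avoid the problem. What the reply does not rescue is the unqualified sentence in the Blinding section, which the design does not meet at the level that is randomized.

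Three further replies also stand.

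- Knowing the group is not knowing the device. A scorer who knows that a form is from Group 1 still does not know which of the three sessions it describes. Replying that no acupuncture was received also leaves little discretion, so the room for judgement lies mainly in remarks and queries.
- For the statistician, seeing three columns against two does not alter a test on scores already fixed. That part of the claim is inaccurate but does not itself produce bias.
- A missing form may also reflect drop-out or an omission, so absence is conclusive only to someone who knows it was planned.

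A reader might also want a bias in percentage points. That would require assuming how far knowledge of the group shifts a scorer's calls. The document gives no basis for such a shift or for its direction.

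**Conclusion.** The point holds at group level. The statement that assessors and statisticians are blind to allocation is broader than the design supports. The group is open to anyone who sees a participant's linked forms, and may be disclosed in conversation to an assessor who questions participants after No treatment.

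Under session-by-session handling the group is certain for about 40% of forms. That figure assumes complete data, 38 per group and equally likely session orders. It becomes all complete records if linked forms are scored together, and none by the form count if forms are scored singly without identifiers.

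The exposure is limited to the two between-group comparisons of blinding rates. The within-group comparisons of real with sham are not unblinded by this route. Whether scoring is biased, and by how much, cannot be determined from the document.

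**What to change.** 1. Record BTQ 1 answers and any remarks verbatim. Have existing blinded personnel score success or failure from single, de-linked forms in a listing stripped of participant, group, session number and device. Lock the scores before labels are attached.
2. Restate the Blinding section: assessors and statisticians are blind to device and session codes until that lock, and no claim is made for group.
3. Reconcile the third BTQ 1 in Study flow with its omission after No treatment, so that the trigger for disclosure and BTQ 2 is clear for Group 2.

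A dummy form after No treatment would equalize the count, but is not advised. Participants know they were untreated and can say so, and an acupuncture questionnaire at that point might prompt the very remarks that the scoring rule counts as failure.

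The cost is a narrower blinding claim and a little extra data handling. No extra staff, participant procedure or change in sample size is needed. Trial status describes the study as recruiting; if that is still so, scoring can be arranged this way before the data are analysed.

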### Intervention

#### Study flow

The study flow will be as follows. Group 1 will consist of Sham ST, Real ST, and PHNT. Group 2 will consist of Real Park, Sham Park, and No treatment. Groups 1 and 2 are separate groups; participants allocated to Group 1 will not receive Real Park, Sham Park, and No treatment and vice versa. Participants will have a total of three sessions (acupuncture or no treatment) in a day (Fig. 1). Before acupuncture treatment, the investigator will explain to participants that they will receive three different types of acupuncture except for the no treatment session. Participants will not know that placebo acupuncture occurred until all sessions are completed. To avoid order effect, the order of the three treatment sessions in each group will be randomly assigned by the CRC. Before the first session, the CRC will collect demographic information (e.g., age, sex) and baseline data (e.g., vital signs, acupuncture expectation questionnaire (AEQ) [6], and bodily sensation questionnaire (BSQ)). After each treatment session, participants will complete the blinding test questionnaire 1 (BTQ 1) and acupuncture sensation questionnaire (ASQ) and will be asked about adverse events (AEs). After completion of the third BTQ 1 and ASQ, an independent assessor will inform the participants of the use of placebo acupuncture and instruct them to complete the blinding test questionnaire 2 (BTQ 2).

**Fig. 1 Fig1:**
[figure not shown]
Study flow. *AEQ* indicates acupuncture expectation questionnaire, *BSQ* bodily sensation questionnaire, *BTQ2* blinding test questionnaire 2, *R* randomization

#### Procedures of each session

Physiological data including heart rate (HR) and skin conductance response (SCR) will be measured by an operator during each session to quantify the autonomic nervous system (ANS) response (Fig. 2). We will record three tonic responses (before, during, and after acupuncture treatment) and one phasic response (during stimulation).Stabilization: After all preparations (e.g., attaching electrodes, checking the ECG and SCR wave patterns) are complete, participants will lie on the bed for 5 to10 min to stabilize.Tonic response before acupuncture: We will measure the tonic ANS response before acupuncture treatment during 5 min of resting.Needle insertion and rest: We will insert the acupuncture needle and induce the de-qi sensation for 1 min and explain to participants that the response induced by needle insertion will be measured. To minimize the influence of the acupuncture insertion, participants will be rested for 1 min.Phasic response during stimulation: The practitioner will approach her hand to the left ST 36 acupuncture point and rotate the needle eight times within 3 min according to an audio signal relayed via a headphone. The stimulation timing will be pseudo-randomly set by computer (Psychtoolbox and Matlab, The MathWorks Inc., MA, USA).Rest: To minimize the influence of the acupuncture stimulation, participants will be rested for 1 min.Tonic response during acupuncture: We will measure the tonic ANS response for 5 min during acupuncture treatment.Needle removal and rest: We will remove the acupuncture needle for 1 min. To minimize the influence of the acupuncture needle removal, participants will be rested for 1 min.Tonic response after acupuncture: We will measure the tonic ANS response for 5 min after the acupuncture needle is removed.

